#### Economic analysis

We will conduct a cost-utility analysis (CUA) and report an incremental cost-utility ratio (ICUR) reflecting the incremental cost per additional QALY gained by participating in the intervention, with and without discounting. Uncertainty will be characterised by probabilistic sensitivity analyses, varying cost inputs in 10,000 Monte Carlo simulations and assessing the probability of IPT being cost-effective at various willingness-to-pay thresholds. The time horizon for accumulating both costs and outcomes will be 30 months (the length of the full trial as well as follow-up) using 1-month time steps, capturing the longest possible timeframe for the intervention effects for which data collection is feasible. An annual discount rate of 3% will be applied to both costs and effects occurring beyond 12 months.

Subsequently we will conduct a benefit-cost analysis (BCA) to provide additional insights relevant for policy considerations. The BCA will use two approaches to valuing outcomes: (1) a human capital valuation approach using Nepal’s national minimum wage, and (2) a valuation of statistical life year approach (VSLY) for Nepal. Each approach will compare the net present value (NPV) of the QALYs gained in each treatment arm. Benefit-cost ratios and net benefits will be calculated for each approach. The probability of intervention vs. control conditions’ having positive NPV under each valuation approach will then be calculated via probabilistic sensitivity analysis with 10,000 replications.

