To estimate indirect costs for the modified societal perspective, we will document productivity loss and informal care costs by recording adolescents’ time spent on intervention-related activities (including travel and participation) if relevant, as well as time and costs associated with outside healthcare utilisation. At endline and follow-up, we will collect data on adolescent health care visits since the baseline survey, including the time and out-of-pocket expense for each visit (across a range of non-school based formal and informal healthcare types available locally). For each type of healthcare service received, we will establish whether its cost is fully covered by out-of-pocket expenditures, or whether it was partially or fully subsidised by the provider. We will record the estimated subsidised cost of services using publicly available information; if subsidised costs are not available, we will contact service providers to establish appropriate estimates or ranges which will be tested in sensitivity analyses. We will collect productivity and informal care costs from interviews with all available parents at endline and follow-up, documenting the time parents have spent providing care as well as opportunity costs of care-seeking for both parents and adolescents. Adolescents will be asked about any earnings from paid work and opportunity costs of healthcare utilisation at midline, endline, and all follow-up surveys. Intervention participants will also be asked about opportunity costs of IPT attendance at midline and endline during group cohesion assessments to maintain masking of group allocation. Cost data will be collected prospectively throughout the trial in Nepali rupees (NPR) and reported in 2024 prices.

The primary health outcome of interest for the economic evaluation analyses is the quality-adjusted life year (QALY). QALYs will be calculated using EQ-5D-5 L health utility scores from adolescents at each planned timepoint for data collection. Using this data, we will derive QALY weights using existing value sets from India, which represent the closest cultural context for which EQ-5D-5 L value sets are available [65].

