The primary outcome of interest, the mean PHQ-A difference between the arms and 95% confidence intervals, will be estimated using mixed effects linear regression to take account of both the clustering due to the unit of randomisation being school and repeated measures by individual. The midline, endline and follow-up measures of the outcome measure are the dependent variable with a random intercept for cluster/school and an unstructured covariance matrix at the level of participant residuals to allow for repeated measures. This mmrm approach is preferred as it avoids model misspecification and is unbiased when data is missing at either random or completely at random [68]. The model will include the baseline measure of PHQ-A (ANCOVA approach), a dummy variable for trial arm, for timepoint and a trial arm by timepoint interaction to allow the treatment effect to vary across time. As randomisation is stratified by wave, this will always be included as a covariate in the analysis model. The model will be estimated using restricted maximum likelihood (REML) allowing the inclusion of all participants, with missing data as ignorable under the assumption of missing at random. Continuous secondary outcomes will be analysed using the same methods. Standardised effect sizes will be calculated by dividing the treatment arm difference estimate by the baseline standard deviation.

Model assumptions will be verified; linear mixed effects models assume residuals are normally distributed at the individual and cluster level and these will be checked appropriate data transformations will be applied if necessary and/or bootstrap procedures appropriate for multilevel models.

Model assumptions will be verified; linear mixed effects models assume that residuals are normally distributed at the individual and cluster level, which will be checked prior to analysis. Appropriate data transformations and/or bootstrap procedures appropriate for multilevel models will be applied if necessary.

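### The cost-utility simulation names only cost inputs as varied, so the probability that IPT is cost-effective leaves out the clustered sampling error in QALYs

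*Protocol article*

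**What the plan says.** Under Economic analysis, the protocol plans a cost-utility analysis that reports an incremental cost per QALY gained (ICUR). On uncertainty it says: "Uncertainty will be characterised by probabilistic sensitivity analyses, varying cost inputs in 10,000 Monte Carlo simulations". The sentence goes on to the output, "assessing the probability of IPT being cost-effective at various willingness-to-pay thresholds". Cost is the only input named.

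The effect side comes from the trial sample. Under Economic evaluation data collection: "QALYs will be calculated using EQ-5D-5 L health utility scores from adolescents at each planned timepoint for data collection". Under Economic analysis: "The time horizon for accumulating both costs and outcomes will be 30 months".

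Three other statements bear on uncertainty:
- For subsidised service costs, Economic evaluation data collection says "we will contact service providers to establish appropriate estimates or ranges which will be tested in sensitivity analyses". This again concerns costs.
- For the benefit-cost analysis, the probability of a positive net present value "will then be calculated via probabilistic sensitivity analysis with 10,000 replications". The varied inputs are not named.
- Under Quantitative analysis, "Continuous secondary outcomes will be analysed using the same methods". If EQ-5D is treated as continuous, this gives it a mixed model with a school random intercept and a confidence interval. Nothing links that model to the economic simulation.

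**The concern.** An ICUR, or the equivalent net benefit, has two estimated parts: incremental cost and incremental QALYs. The probability of cost-effectiveness should reflect the uncertainty in both. If only costs vary, every replicate uses the same QALY difference, and the result answers a narrower question: how likely IPT is to be cost-effective if the QALY effect equals its point estimate.

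The part left out is the one that randomisation estimates. The QALY difference rests on 46 analysable schools by the protocol's own reckoning, and school clustering applies to it as it does to PHQ-A.

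Cost-utility is part of the stated aim and is the third objective. The Discussion makes possible scale-up through the education system depend on IPT being shown to be cost-effective. The probability by threshold is the figure a policymaker is likely to read first.

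**Working it through.** The protocol states no cost-effectiveness probability, so there is none to reproduce. The check shows what leaving out QALY error does, using the document's figures where they exist and declared assumptions elsewhere.

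**From the protocol**
- 46 schools with an average of 12 analysed (Power and sample size), so 23 × 12 = 276 per arm.
- Design effect 1.79 (ICC 0.07) or 1.34 (ICC 0.03). With cluster-size CV 0.16: 1 + ((1 + 0.16²) × 12 − 1) × 0.07 = 1.792; with 0.03 it is 1.339. Both reproduce. They were derived for PHQ-A at endline; applying them to QALYs is an assumption.
- Unit cost USD 96.9 from the feasibility study (Interpersonal therapy), used here as the incremental cost.

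**Assumed, because not given:** QALY gain, SD of individual QALYs, standard error of cost, and threshold. Cost and QALY errors are taken as independent, with no adjustment for baseline utility.

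**Formulas.** Net benefit = λ × ΔQ − ΔC. SE(ΔQ) = SD × √(2 × DE / 276), where √(2 × 1.79 / 276) = 0.1139. P(cost-effective) = Φ(mean net benefit / SD of net benefit).

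**Illustration A.** ΔQ = 0.02, λ = 1.5 × 96.9 / 0.02 = USD 7,268 per QALY, cost SE 10% = 9.69. Mean net benefit = 0.5 × 96.9 = 48.45.
- Costs only: Φ(48.45 / 9.69) = Φ(5) = 1.00.
- QALY SD 0.06: λ × SE(ΔQ) = 49.66; Φ(48.45 / √(9.69² + 49.66²)) = 0.83.
- QALY SD 0.09: λ × SE(ΔQ) = 74.49; Φ(48.45 / √(9.69² + 74.49²)) = 0.74.
- With design effect 1.34 the last two become 0.86 and 0.77.
- With cost SE 30% = 29.07, costs only gives Φ(48.45 / 29.07) = 0.95; adding QALY error (DE 1.79) gives 0.80 and 0.73.

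**Illustration B.** Design effect 1.79, cost SE 20% = 19.4, QALY SD 0.10 to 0.45:

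| ΔQ | Threshold (USD) | Costs only | Costs and QALYs, SD 0.10 → 0.45 |
|---|---|---|---|
| 0.04 | 4,000 | 0.999 | 0.90 → 0.62 |
| 0.08 | 1,400 | 0.78 | 0.73 → 0.58 |
| 0.02 | 4,000 | 0.19 | 0.37 → 0.47 |
| 0.08 | 4,000 | 1.00 | 1.00 → 0.86 (0.99 at SD 0.20) |

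The third row shows the error running the other way: costs alone understate the probability. The fourth shows that the gap can be negligible when the ICUR is well below the threshold and QALY variance is modest.

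**Direction.** With independent errors, QALY error always widens net benefit and so moves the probability towards 0.5. With correlation ρ, the added variance is (λ·SE_Q)² − 2ρ·λ·SE_Q·SE_C, which is negative only if λ·SE_Q < 2ρ·SE_C. Hence *generally* rather than *always*, and hence the need to keep the correlation.

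**The case against.** The strongest reply is that the sentence does not contain the word *only*, and that a journal article condenses a fuller health-economic plan in which QALYs may well be sampled. That would be a full answer if the article had said just that a probabilistic sensitivity analysis would be done. It names the varied inputs instead, and leaves out the one estimated from trial outcomes. If a fuller plan does sample QALYs, this sentence misdescribes it and still needs correcting.

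Other points on that side stand and limit the claim:
- **A reader might infer that the acceptability curve will be close to a step function, or far too certain.** The document does not support that. Costs are not shown to be nearly certain: salaries and pilot costs must be allocated between arms, and the modified societal perspective adds out-of-pocket, productivity and informal care costs. At an assumed 30% cost SE, the costs-only figure is already 0.95 rather than 1.00.
- **A reader might infer a much larger gap at the 30-month horizon.** Raising the QALY SD to 0.25 to 0.375 while leaving the gain at 0.02 gives 0.59 to 0.56, but this assumes no gain after week 32. Scaling the gain to 0.08 as well, with the threshold again 1.5 × ICUR (USD 1,817), gives 0.82 to 0.73.
- **A reader might infer that the benefit-cost simulation also fixes QALYs.** Its sentence, "calculated via probabilistic sensitivity analysis with 10,000 replications", names no varied inputs, so it shows neither that they are fixed nor that they vary.
- The primary PHQ-A analysis, trial conduct and data collection are unaffected, and quality of life may still get its own clustered interval.

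**Conclusion.** The point holds as a fault in a stated rule. The cost-utility uncertainty analysis names only cost inputs, while the QALY difference is a clustered trial estimate whose error is not brought into the simulation anywhere in the article. The resulting probability is conditional on the QALY effect being known and is generally too far from 0.5, on whichever side it falls. That direction follows from the method, provided cost and QALY errors are not strongly positively correlated.

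The size is not determined by the document. Under assumed inputs it ranges from negligible to several tenths of probability, and it is largest when the ICUR is near the threshold or QALY variance is high. The figures above are illustrations, not forecasts. The issue affects one of four objectives and can be settled in wording before the economic analysis.

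**What to change.** Amend the sentence under Economic analysis so that each of the 10,000 replicates draws incremental cost and incremental QALYs jointly, keeping their correlation and the school clustering. Two suitable ways:
- a bivariate multilevel model for cost and QALYs with a school random effect, adjusted for wave and baseline utility; or
- a cluster bootstrap with a small-sample correction. A plain resample of schools within arm and wave would not do. Six schools per wave at 1:1 leave three per cell, and resampling three reproduces only 2/3 of the between-school variance, so that component's SE is √(2/3) = 0.82 of its proper value, about 18% too small.

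Keep the variation in cost inputs and in cost allocation on top of the joint draws; the main provider costs are allocated by arm and may not exist as individual values. State that the ICUR interval and the acceptability curve come from these draws, and that the benefit-cost simulation, whose varied inputs are now unnamed, uses the same ones.

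The cost is a little more analysis work and a change of wording. No new data are needed. The acceptability curve will look less certain. Recruitment is expected to run to November 2026 and the horizon is 30 months, so there is time to pre-specify this.

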#### Public and policy involvement

Our protocol is informed by several stakeholder groups. We adapted IPT for adolescents in Nepal through formative research with adolescents, parents, teachers and health workers in Nepal. We assessed the feasibility and acceptability of the intervention through qualitative interviews with the same stakeholder groups.

In the pilot cRCT, we piloted methods for this phase III cRCT and sought feedback from stakeholders on their acceptability. The interim qualitative and quantitative findings from the trial were presented to our TSC consisting of local Nepali and international experts. These findings informed the study procedures of the current protocol (e.g., screening procedures, inclusion and exclusion criteria, safety protocols, survey timing, survey battery, mechanism hypotheses). The same TSC will continue to meet throughout the Phase III trial. We will also convene a DMC to monitor the progress of the trial.

To input on the protocol and advise on trial issues, we have convened a youth advisory board in the study setting comprising ~ 8 local adolescent boys and girls who participated in the pilot cRCT.

#### Ethical issues

We have ethical approval from the Nepal Health Research Council (approval no. 2144) and University College London Research Ethics Committee (project ID 0351).

At the school level, we will seek permission to conduct the study from the school principal. Eligible adolescents who wish to participate in the trial will be asked to take home a written information sheet and consent form. We will obtain written consent from adolescents which will be collected before the baseline survey is conducted. For adolescents aged 17 and younger, we will take consent from their caregiver and adolescent assent. We will obtain consent for all adult participants from whom we collect data (e.g. teacher, IPT facilitator, parent).

We anticipate disclosures of suicidality at screening and throughout the trial. We have therefore developed a standard operating procedure (SOP) to manage these cases. This involves assessment by a psychosocial counsellor and referral to local mental health services where required. There is a separate SOP for disclosures of abuse which includes safety assessment and planning and potential referral to the Women, Children and Social Inclusion Section attached to the local municipality, or to a hospital where physical and mental health problems can be further assessed and managed.

#### Dissemination

We will proactively share findings with schools and advisory boards by developing simple research summaries, supported by workshops where requested. In Chitwan and Kathmandu we will hold workshops to disseminate findings to policy makers and relevant organisations. We will disseminate findings to academic audiences through publication in international peer-reviewed journals, and presentation at conferences. We will also hold a webinar for global policy makers and academics.

#### Trial status

Participant recruitment started for Wave 1 on May 15th 2025. The expected date for completion of recruitment is 30th November 2026 (Wave 8). IPT started for Wave 1 participants in June 2025 and for Wave 2 participants in July 2025.

## Discussion

We will conduct the first realist cluster-randomised controlled trial of a psychological intervention in a LMIC and help to address a key research gap about how these interventions work and their long-term effects. Moreover, we will contribute to scant evidence for the effectiveness of school based psychological interventions in LMICs. If our trial shows IPT is cost-effective, we envisage the intervention could be scaled up through the education system in Nepal. IPT would therefore be a vital component of a comprehensive model of school-based mental health care, aligning with the National Mental Health Strategy and Action Plan 2020 which includes integrating mental health topics in school curricula and providing mental health training for teachers and parents. Through our realist trial design, we will build evidence-based mid-range theories about intervention processes and how they can be modified and shaped by context. Researchers and policymakers from outside Nepal can then use this information to decide whether IPT might also be useful and effective in their context.

Our study has various strengths. We build on extensive formative research, piloting and stakeholder engagement, which confirmed the feasibility of our intervention and study design. We will use rigorous methods to mitigate bias including conducting randomisation after the baseline survey to reduce selection bias, masking research assistants to mitigate detection bias and publishing our statistical analysis plan to prevent reporting bias.

The study also has limitations. First, implementing the trial in the Nepali education system is challenging. Schools often close at short notice due to staff strikes, heat and public holidays. These closures will impact the trial timeline, for example delaying randomisation, survey administration or IPT sessions, although schools in control and intervention arms are likely to be equally affected. Second, although cluster randomisation minimises contamination and is more acceptable and feasible than individual randomisation, it decreases the likelihood of balancing individual participant characteristics across trial arms. Third, in trials of psychological interventions, it is inherently impossible to mask participants to allocation. Intervention participants may show improved mental health outcomes because they know they are receiving IPT (known as the Hawthorne Effect), which could potentially lead to overestimation of intervention effects. To mitigate this effect, we will match the survey burden across trial arms to the extent that it is possible, conduct long term follow-up to explore whether effects persist beyond the trial period and use objective outcome measures where feasible including school attendance and examination grades. Fourth, trials of psychological interventions with treatment as usual or waitlist controls have been criticised because these control conditions do not match hours of therapist contact in the intervention arm and it is therefore impossible to test whether an intervention is effective because of its specific techniques or because of generic effects such as supportive human contact [70]. To address this criticism, we will implement an enhanced control condition with assessment and referral for high-risk cases and capacity building in local clinics. Moreover, our realist design will enable us to examine mechanisms through which IPT improves depression including specific techniques and general elements.

In conclusion, this realist cRCT of school-based group IPT has the potential to generate robust evidence for the effectiveness of psychological interventions in Nepal and will help to inform translation and optimisation of these interventions in other low-resource settings.

## Data Availability

No datasets were generated or analysed during the current study.

## Abbreviations

95% CI: 95% confidence interval
CMOCs: Context–mechanism–outcome contingencies
(c)RCT: (Cluster) randomised trial
CSSRS: Columbia Suicide Severity Rating Scale
DMC: Data Monitoring Committee
DSRS: Depression Self–Rating Scale
EQ: 5D–EuroQol–5 Dimension 5 levels
GAD: 7–Generalised Anxiety Disorder–7
IPT: Interpersonal psychotherapy
IPT: A–Interpersonal psychotherapy modified for adolescents
ITT: Intention to treat
LMICs: Low–and middle–income countries
mhGAP: WHO mental health GAP Action Programme
MRC: Medical Research Council
PCL: 5–Post–Traumatic Stress Disorder Checklist for DSM–5
PHQ: A–Patient Health Questionnaire modified for adolescents
PRIME: PRogramme for Improving Mental health care
PTSD: Post–traumatic stress disorder
SEE: School Education Exam
SES: Standardised effect size
SOP: Standard operating procedure
TPO Nepal: Transcultural Psychosocial Organization Nepal
TSC: Trial steering committee
UCL: University College London
UKRI: UK Research and Innovation
UNICEF: United Nations Children’s Fund
US: United States
WHO: World Health Organization
